## Abstract

**Background:**

Consumption of alcohol is synonymous with military populations, and studies have shown that serving personnel drink more than age- and sex-matched civilian populations. While ingrained in the military culture, excessive alcohol use is associated with increased rates of disciplinary issues, sickness absence, and loss of productivity, as well as contributing to a burden of acute and chronic health problems. Alcohol brief interventions can reduce alcohol use in civilian populations, but there is a paucity of evidence relating to the effectiveness of similar interventions in military populations. The DrinksRation smartphone app was designed to have a basis in behavior change technique theory and focuses on providing interactive behavioral prompts tailored to a military population. It has previously been shown to be effective in a help-seeking veteran population.

**Objective:**

The primary aim of the Military DrinksRation randomized controlled trial study is to determine whether it is similarly effective in a serving military population.

**Methods:**

We compare the effectiveness of the DrinksRation smartphone app with treatment as usual for personnel identified at risk of alcohol-related harm using the Military DrinksRation study that is a 2-arm, single-blind, 1:1 randomized controlled trial of the UK Armed Forces population. It is hypothesized that the DrinksRation app will be more efficacious at reducing alcohol consumption compared to treatment as usual. Recruitment will be predominantly from routine, periodic dental inspections all service personnel regularly undertake, supplemented by recruitment from military-targeted media messaging. The primary outcome is the change in alcohol units consumed per week between baseline and day 84, measured using the timeline follow-back method. Secondary outcome measures are a change in the Alcohol Use Disorders Identification Test score, a change in the quality of life assessment, and a change in drinking motivations and app usability (intervention arm only) between baseline and day 84. A final data collection at 168 days will assess the persistence of any changes over a longer duration.

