### Intervention

Participants randomized to the intervention arm of the RCT will be sent an email link to the DrinksRation app with a unique reference code to enable data linkage between REDCap and DrinksRation. The app’s function, theoretical basis, and supporting evidence are fully described elsewhere [16,20,24]. Images of the app and its functionality are shown in Figure 1. After downloading the app, on first use, participants will be prompted to complete baseline assessment surveys. App usage and further surveys were then presented by the app with push notifications to the participant, highlighting the need for completion. Participants will be asked to use the app for a minimum of 28 days. Participant flow through the study is shown in Figure 2.

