**Figure 2 figure2:**
[figure not shown]
Study flow diagram. Primary and secondary outcomes are assessed at day 84, with outcomes reassessed at day 168 in order to understand the longer-term benefits of the intervention. AUDIT-C: Alcohol Use Disorders Identification Test for Consumption; REDCap: Research Electronic Data Capture.

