### Measures

The primary outcome measure is a change in alcohol units consumed per week between baseline and day 84, as measured by the timeline follow-back method [27]. Secondary outcomes are a change in the Alcohol Use Disorders Identification Test (AUDIT) score, a change in the quality of life assessment, and a change in drinking motivations and app useability. While the DrinksRation intervention aims to reduce alcohol intake at 84 days, a final data collection at 168 days will assess any persistent benefits.

Data will be collected through a selection of surveys pushed to the participants in line with the periodicity detailed in Table 1.

The study instruments are all validated for the general population and are detailed in Table 1. The alcohol and mental health symptomatology surveys were included in the veteran’s trial. The MDR trial additionally includes surveys for drinking motivations (Drinking Motives Questionnaire 9-item tool [DMQ-R]), recent life events (Recent Life Events Questionnaire [RLE-Q]), gambling motives (Gambling Motivations Questionnaire [GMQ-9]), and domestic abuse and sexual assault (National Crime Survey for England and Wales). These behaviors have been associated with both alcohol consumption [3] and a military population [40,41]. A tertiary outcome of the MDR study is to assess the correlation of these issues with alcohol use within the military population. This information does not contribute to the assessment of the app’s effectiveness, but it is valuable information for UK defense policy makers.

**Table 1 table1:** Summary of measures and data collection time points.

Measure	Total questions	Day 0	Day 0-1	Day 3	Day 7	Day 28	Day 84	Day 168
Demographics	18	✓						
AUDIT-C^a^ [13]	3	✓						
Participation information and consent	N/A^b^	✓						
Alcohol use (AUDIT^c^) [28]	10		✓			✓	✓	✓
Alcohol intake (TLFB^d^) [27]	N/A		✓			✓	✓	✓
Resource allocation (YAACQ^e^) [29]	24		✓				✓	✓
Readiness to change ruler	1		✓					
Self-efficacy ruler	1		✓					
Depression (PHQ-2^f^) [30]	2		✓			✓		
Anxiety (GAD-2^g^) [31]	2		✓			✓		
International trauma questionnaire for PTSD^h^ (PC-PTSD-5^i^) [32]	5		✓			✓		
World Health Organization Quality of Life-BREF^j^ (WHOQOL-BREF) [33]	27			✓		✓	✓	✓
Loneliness (De Jong Gierveld) [34]	11			✓		✓		
Drinking motivations (DMQ-R^k^) [35]^l^	20			✓			✓	
Recent life events (RLE-Q^m^) [36]^l^	21			✓				
Gambling motives (GMQ-9^n^) [37]^l^	9				✓			
Domestic abuse (NCSE&W^o^) [38]^l^	30				✓			

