Sexual assault (NCSE&W) [38]^l^	13				✓			
mHealth App Usability Questionnaire (MAUQ) [39]	16					✓		
Approximate time to answer (min)^p^	—^q^	10	13	15	9	20	15	15

^a^AUDIT-C: Alcohol Use Disorders Identification Test for Consumption.

^b^N/A: not applicable.

^c^AUDIT: Alcohol Use Disorders Identification Test.

^d^TLFB: timeline follow-back.

^e^YAACQ: Young Adult Alcohol Consequences Questionnaire.

^f^PHQ-2: Patient Health Questionnaire 2-item tool.

^g^GAD-2: Generalized Anxiety Disorder 2-item tool.

^h^PTSD: posttraumatic stress disorder.

^i^PC-PTSD-5: Primary Care-Posttraumatic Stress Disorder 5-item screening tool.

^j^BREF: Best Available Technique Reference Document.

^k^DMQ-R: Drinking Motives Questionnaire 9-item tool.

^l^Not included in veterans’ DrinksRation study.

^m^RLE-Q: Recent Life Events Questionnaire.

^n^GMQ-9: Gambling Motivations Questionnaire.

^o^NCSE&W: National Crime Survey for England and Wales.

^p^Allowing 10 seconds per question, rounded up and with additional comfort time added.

^q^Not available.

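### All three are defined as change from baseline to day 84, but app usability has no computable change, and quality of life and drinking motives have no pre-intervention baseline

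*Protocol article*

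**What the plan says.** **Outcome definitions.** After AUDIT and quality of life, the Abstract (Methods) lists "a change in drinking motivations and app usability (intervention arm only) between baseline and day 84". The Measures section repeats the list as "a change in the quality of life assessment, and a change in drinking motivations and app useability" and gives no other time window. The Figure 2 legend says: "Primary and secondary outcomes are assessed at day 84, with outcomes reassessed at day 168".

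**Schedule (Table 1).**
- WHOQOL-BREF, 27 questions: Days 3, 28, 84 and 168.
- DMQ-R, 20 questions: Days 3 and 84.
- MAUQ (usability), 16 questions: Day 28 only.
- For contrast, AUDIT and timeline follow-back start in the Day 0-1 column.

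**Order of events.** The Recruitment section randomises participants once they have consented and given demographics. For the app arm, the Intervention section says "After downloading the app, on first use, participants will be prompted to complete baseline assessment surveys", and next "App usage and further surveys were then presented by the app with push notifications to the participant". Controls get their surveys by email (Control section).

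**Status of DMQ-R.** The Measures section lists drinking motivations as a secondary outcome. It then groups DMQ-R with the surveys added since the veterans' trial, whose correlation with alcohol use is called a tertiary outcome and is said to play no part in judging whether the app works.

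**The concern.** A change from baseline to day 84 needs a value at each end, and the first should precede any effect of treatment. By Table 1, usability has neither value. Quality of life and drinking motives have the day-84 value, but their earliest value comes after randomisation and, in the app arm, after app use has begun.

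Two things are at stake. First, one named secondary outcome cannot be reported as defined. Second, for the other two an analyst would probably take Day 3 as the baseline because it is the only early value. That choice builds a post-randomisation measurement into the treatment contrast. A later analysis plan can choose among the data collected, but it cannot supply measurements that were never scheduled.

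**Working it through.** **1. Are the tick positions read correctly?** Table 1 carries its own check: a row of estimated completion times, built at 10 seconds per question plus comfort time. Minutes = questions × 10 / 60.

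| Visit | Questions as ticked | Minutes | Stated |
|---|---|---|---|
| Day 0-1 | 10+24+1+1+2+2+5 = 45 | 7.5, plus timeline follow-back | 13 |
| Day 3 | 27+11+20+21 = 79 | 13.2 | 15 |
| Day 28 | 10+2+2+5+27+11+16 = 73 | 12.2, plus timeline follow-back | 20 |
| Day 84 | 10+24+27+20 = 81 | 13.5, plus timeline follow-back | 15 |

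The ticks as read fit the stated times. The alternatives fit worse:
- Day 3 without WHOQOL-BREF and DMQ-R: 79 − 47 = 32 questions, 5.3 min against 15 stated.
- Day 0-1 with both added: 45 + 47 = 92 questions, 15.3 min before timeline follow-back, above the 13 stated.
- Day 84 with MAUQ added: 81 + 16 = 97 questions, 16.2 min before timeline follow-back, above the 15 stated.

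Comfort time varies between visits, so this supports the reading without proving it.

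**2. Which values exist for a change from baseline to day 84?**

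| Instrument | Day 0 or Day 0-1 | Day 84 | What can be formed |
|---|---|---|---|
| MAUQ | no | no | a Day-28 score only |
| WHOQOL-BREF | no | yes | change from Day 3; day-84 comparison |
| DMQ-R | no | yes | change from Day 3; day-84 comparison |

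The Figure 2 legend also promises reassessment at day 168. WHOQOL-BREF is collected then; DMQ-R and MAUQ are not.

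**3. What does a Day-3 reference do?** Let D(t) be the expected difference between arms (app minus control) at time t. Before treatment, randomisation makes D(pre) = 0.
- Change from a pre-randomisation baseline estimates D(84) − D(pre) = D(84).
- Change from Day 3 estimates D(84) − D(3).

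The discrepancy is D(3), subtracted one for one. If an early benefit persists to day 84, the estimate moves towards no effect. The article gives nothing from which to put a value on D(3), so no size is claimed.

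**4. Who supplies a Day-3 value?** In the app arm a participant must have downloaded the app and answered a push notification. In the control arm a participant need only answer an email. Each arm gets one reminder after 24 hours and no further chasing (Data Monitoring section). The response route differs by arm, so the set of responders may differ too.

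**5. Cost of earlier collection.** 27 + 20 = 47 questions; 47 × 10 / 60 = 7.8 min. Day 0 goes from the stated 10 min to about 18, and Day 3 falls to 32 questions (5.3 min) if the two instruments are moved rather than repeated. The article calls DMQ-R a 9-item tool but counts 20 questions in Table 1. With 9 items the cost would be 36 × 10 / 60 = 6.0 min, so 7.8 is the upper figure.

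**6. Sample size.** The stated figures rest on the primary outcome alone. Assuming 80% power and a two-sided 5% test, n = 2 × (1.960 + 0.842)² × 14.9² / 4² = 217.8, rounded up to 218 per arm. Then 218 / 0.6 = 363.3, rounded up to 364 per arm, or 728 in total, as stated. No secondary outcome enters.

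**The case against.** A reader might infer that three secondary outcomes cannot be computed. The documents support that only for usability. For quality of life and drinking motives, both a change from Day 3 and a day-84 comparison are available. The article does not tie the word baseline to a particular day for each instrument, and Figure 2 is not shown. Even so, calling Day 3 the baseline leaves it after randomisation and after first app use.

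The usability wording can also be read as two items, with change attached only to drinking motivations. That removes the impossible change score, but it leaves a secondary outcome said to be assessed at day 84 and collected only on Day 28.

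A reader might also infer that responders on Day 3 do differ by arm. That is not shown. A missed survey does not stop later prompts, and mixed models are planned for quality of life, so a missing Day-3 value need not exclude a participant. It remains a risk. Three days may also be too short for a material effect on either measure, and nothing in the article says otherwise.

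A planned DMQ-R treatment effect should not be taken for granted, since the analysis section names mixed models only for AUDIT and quality of life among the secondary outcomes.

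Finally, AUDIT and timeline follow-back at Day 0-1 also follow randomisation and, in the app arm, are completed at first use of the app. They are nonetheless the designated baseline surveys, taken as use begins and not days into it. The Day-3 problem does not carry over to them.

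**Conclusion.** The outcome definitions and the schedule contradict each other, and the article should be corrected. The fault differs in degree:
- **Usability:** neither of the two required values is collected, so no change and no day-84 value can be reported.
- **Quality of life and drinking motives:** no pre-intervention value exists. A change from Day 3 is computable but loses any app effect already present on Day 3. That loss is of unknown size and possibly small. Arm-dependent response on Day 3 is an added risk.
- **DMQ-R:** its status as secondary or tertiary is inconsistent within the Measures section.

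This rests on the tick positions in Table 1, which the table's completion times support, and on the stated order of randomisation, first app use and later surveys. The primary outcome, AUDIT and the sample size are unaffected.

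**What to change.** 1. **Preferred:** collect WHOQOL-BREF on Day 0 before randomisation, and DMQ-R with it if drinking motivations stay a secondary outcome. This adds up to 47 items, about 8 minutes, at entry. The longer entry survey may deter some people.
2. **Otherwise**, and for anyone already enrolled: define these two outcomes as comparisons between arms at day 84, with the Day-3 value used neither as baseline nor as covariate. No new data are needed. The cost is the precision that a true baseline would have given, which depends on a correlation the article does not report.
3. **Usability:** restate it as a single descriptive Day-28 score in the intervention arm, and take it out of the outcomes described as changes or assessed at day 84.
4. **DMQ-R:** state once whether it is secondary or tertiary, and bring the Abstract, the Measures section and the Figure 2 legend into line with Table 1.

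Leave PHQ-2, GAD-2 and PC-PTSD-5 where they are. Moving them later to make room would free only 2 + 2 + 5 = 9 items (1.5 min), and at Day 0-1, not Day 0. It would also give measures that are repeated on Day 28 the same late reference, and survey answers suggesting mental health problems feed the adverse event review.

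The administrative cost is an amendment through the registry and ethics committee, which the Ethical Considerations section provides for. Option 1 also needs a schedule edit in REDCap and the app.

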**Results:**

The study is expected to open in August 2023 and aims to enroll 728 participants to allow for a study sample size requirement of 218 per arm and a 40% attrition rate. It is expected to take up to 12 months to complete. The results will be published in 2024.

**Conclusions:**

The Military DrinksRation study will assess the efficacy of the smartphone app on changing alcohol use behaviors in service personnel. If a positive effect is shown, the UK Defence Medical Services would have an effective, evidence-based tool to use as part of an alcohol management clinical pathway, thereby providing better support for military personnel at risk of harm from alcohol drinking.

**Trial Registration:**

ISRCTN Registry 42646;. https://doi.org/10.1186/ISRCTN14977034

**International Registered Report Identifier (IRRID):**

PRR1-10.2196/49918

## Introduction

### Overview

Consumption of alcohol is highly prevalent in the United Kingdom, with 65% of men and 50% of women reporting having consumed an alcohol-containing drink in the past week [1]. Consumption in the general population has steadily risen since the 1950s, with the most significant increase among women [2,3]. Exploration of drinking trends across the United Kingdom suggests that there has been an overall small reduction in intake in recent years. However, this is due to moderate reductions in the prevalence of drinking (from 70% to 60%) and alcohol intake in young men aged 16-24 years [2]. This reduction masks a 3 unit per week increase in alcohol intake and an increase in the prevalence of drinking by women. While there has been a reduction in the number of drinkers and the amount consumed by the 16-24-year-old age group, they are the group most likely to binge drink, a trend that transfers into the military population. A large cross-sectional study demonstrated that UK military personnel consume alcohol at rates higher than age- and sex-matched civilian personnel [4]. Military personnel are additionally more likely to drink excessively [4,5]. This binge pattern is attributed to the populations being “young single individuals [who] are less likely to have children and other domestic responsibilities that make heavy drinking less frequent or possible” [4] and the military culture of communal risk-taking [5].

Alcohol’s negative effects are wide-ranging and associated with harm to health, accidents, criminality, social disruption, and poor occupational outcomes [1]. For those aged 15-49 years in England, alcohol misuse is the single largest risk factor for ill health and premature death [3]. UK defense data suggest that 59% of military personnel are at risk of alcohol-related harm, which is higher than the general population (42%) [6]. Alcohol was linked to, or the cause of, almost 5% of aeromedical evacuations between 2018 and 2019, and the number of personnel with an alcohol abuse or misuse read code in their primary care clinical notes increased from 457 to 584 between November 2017 and April 2019 [6]. From a health perspective, alcohol is implicated in much of the mental health burden within defense primary health care (DPHC) and complicates other health-related activity through interactions with medication, treatments, and direct exacerbation of symptoms [6,7].

Alcohol is implicated in military disciplinary issues [8,9] and occupationally, alcohol misuse is associated with a loss of productivity, in a dose-dependent manner, through increased rates of sickness absence and presenteeism [3,5]. The occupational impacts of alcohol on the military are more extensive than in the civilian workforce due to the nature of military employment [4,5]. Recognizing the impact that alcohol has on the effectiveness of military personnel, there are various strategies aimed at reducing their alcohol use. Personnel aged 30 years or younger have mandatory alcohol lectures that highlight the harmful effects of excessive consumption and disciplinary issues complicated by alcohol attracting more significant punishment [10].

National guidance recommends alcohol brief interventions (ABIs) for patients identified as consuming alcohol at hazardous or harmful levels [11]. An ABI is “a simple intervention aimed at individuals who are at risk through drinking above the guidelines but are not typically seeking help for an alcohol problem” [12]. All UK Armed Forces (AF) personnel are screened for risky drinking behaviors using the Alcohol Use Disorders Identification Test for Consumption (AUDIT-C) [13] at periodic dental inspections (PDIs). A “brief intervention” is given to personnel who record a score of 4 or more (men) or 3 or more (women). There is concern, however, that recent apparent reductions in alcohol intake reflect reporting bias rather than an actual reduction in the AUDIT-C score. An intentionally low misrepresentation of actual intake would avoid the individual being given an ABI or offered a referral to the general practitioner [14] and avoid any associated concerns about the career impact of being identified as being at risk of harm from drinking.

Existing evidence for the effectiveness of ABIs appears robust, with an extensive Cochrane review determining they can reduce alcohol consumption by 2 standard drinks per week after a year [15]. However, this defined an ABI as “a conversation comprising 5 or fewer sessions of brief advice or brief lifestyle counseling and a total duration of less than 60 minutes” [15]. This exceeds the time available for opportunistic ABIs within DPHC consultations. The Cochrane review also excluded digital interventions, which are intuitively of huge relevance in a young, digital native population such as the AF. Face-to-face interventions may be effective, but not if they are not accessed by a digital generation [16-18]. A narrative review of 10 studies involving military personnel and veterans found that web-based interventions may be of benefit [19]. There remains a paucity of evidence available for the effectiveness of ABIs on military populations, or indeed, for which aspects of behavior change theory are effective in a population with rigid command structures and regulations.

The primary purpose of the DrinksRation randomized controlled trial (RCT) study is to determine whether similar effectiveness is found in a serving military population.

### Military DrinksRation (MDR) Study Aim

DrinksRation is a military-focused smartphone app that has been shown to be effective in reducing alcohol consumption in a veteran, help-seeking population [20]. The primary purpose of this RCT is to determine whether the DrinksRation app has similar effectiveness in a serving, non–help-seeking military population. An effective app could support or integrate into the defense alcohol management pathways and provide support to service personnel while they wait for specialist intervention from defense community mental health services. Additionally, if the links between drinking behaviors and social and health outcomes are better understood, there is scope for future policy design to target the precipitating factors leading to a more positive and healthy life.

## Methods

### Ethical Considerations

This study was approved in September 2023 by the Ministry of Defence Research Ethics Committee (MODREC; registration number: 2154/MODREC/22) and registered as a clinical trial with the International Standard Randomised Controlled Trial (ISRCT) number registry (submission number: 42646). Any amendments to the protocol will be registered with ISRCT and approved by MODREC.

### Study Design

The MDR study is a 2-arm, single-blind, 1:1 RCT of the UK AF population comparing the effectiveness of the DrinksRation smartphone app with treatment as usual (TAU) for those at risk of alcohol-related harm. It is hypothesized that the DrinksRation app will be more efficacious at reducing alcohol consumption compared to TAU.

